## Abstract

**Introduction:**

As infertility incidence increases gradually, frozen–thawed embryo transfer (FET) techniques are continuously being developed and enhanced. Although endometrial preparation regimens are strongly linked to live birth rates (LBR), there has been controversy over the ideal regimen. Hormone replacement therapy (HRT) cycles, despite the ease of synchronizing embryo thawing and embryo transfer timing, increase the risk of pregnancies and obstetric complications compared to natural cycles (NC). By ensuring the presence of the corpus luteum while reducing the number of monitoring sessions, the progesterone modified natural cycle (P_4_mNC) offers more convenience for the patient than the normal NC. This study is designed to compare the effects of P4mNC and HRT cycles on FET outcomes.

**Methods and analysis:**

This study is a single-center, open-label, randomized controlled trial (RCT) targeting to recruit a total of 672 women, with 336 individuals each in two arms (1:1 treatment ratio). Women undergoing in vitro fertilization (IVF) scheduled for a single frozen–thawed blastocyst transfer (FBT) and who have regular menstrual cycles are eligible. After signing an informed consent form, patients will be randomized into two groups: the P4mNC group and the HRT group. The primary objective is to determine whether P_4_mNC-FBT is non-inferior to standard HRT-FBT in terms of LBR. Intention-to-treat analysis will be used for data analysis.

**Ethics and dissemination:**

This study is approved by the Institutional Review Board of the Affiliated Hospital of Shandong University of Traditional Chinese Medicine (Reference No. 2024-144-KY). The results of our study will be submitted to reproductive medicine conferences and journals.

**Clinical trial registration:**

ClinicalTrials.gov, identifier NCT06644794.

## Highlights

This is the first and largest randomised controlled trial to date to examine the clinical outcomes between P_4_mNC and HRT for FBT.This is a RCT that focuses primarily on LBR, but also assesses maternal and neonatal outcomes as well.This is an open-label trial and only targets infertile women with regular ovulation.

## Introduction

A global population survey estimates that 186 million people suffer from infertility (1). As couples postpone childbearing, infertility incidence will gradually increase (2). Thus, infertility poses a persistent reproductive problem worldwide (1). As a result, this has driven advances and improvements in assisted reproductive technology (ART) (3). As vitrification freezing has been introduced and reliable safety data have been validated, the proportion of FET cycles has increased (4–7). There are currently several protocols for endometrial preparation, including true natural cycle (NC) with spontaneous ovulation, modified natural cycle (mNC) with human chorionic gonadotropin (hCG)-triggered ovulation, ovarian stimulation cycles, and hormone replacement therapy (HRT) cycles with or without gonadotropin-releasing hormone agonist (GnRH-a) downregulation (8). Nevertheless, the topic of the optimal protocol for endometrial preparation continues to be controversial (9, 10).

During HRT cycles, embryo thawing and transfer can be coordinated easily. However, recent findings suggest pregnancies resulting from anovulation without the corpus luteum (CL) in HRT cycles may pose potential risks, including an increased likelihood of preeclampsia, preterm birth, and low birth weight, to the mother and fetus compared to NC (11, 12). These differences are probably due to the lack of vasoactive substances produced by the CL (13, 14). As a result, the NC protocol is simpler and more physiologic, and it is more commonly used for endometrial preparation for FET in patients with regular menstruation and normal ovulation (15). However, NC-FET has the disadvantage of being less flexible as it requires more frequent clinical visits to closely monitor follicular development, endometrial thickness, and hormone levels (16). In contrast, mNC is very similar to NC, but ovulation is triggered by hCG, which allows for less frequent monitoring and more convenience for patients, but still requires regular monitoring with ultrasound and serum luteinizing hormone (LH) levels (16, 17). New protocols for endometrial preparation are crucial to enhance the flexibility of FET planning while maintaining ovulation and the presence of the CL. Recently, a retrospective cohort study showed that no inferiority of the P_4_mNC-FBT cycle was detected in terms of clinical pregnancy rate, miscarriage rate, and LBR compared with the HRT-FBT cycle (18). Therefore, we designed this randomized controlled trial (RCT) to further validate the efficacy and safety of the P_4_mNC as endometrial preparation protocol in FBT.

## Objectives

### Primary objective

The primary objective of the study is to investigate if P_4_mNC-FBT is non-inferior to standard HRT-FBT in terms of LBR. ITT and per-protocol (PP) analyses will be performed with a non-inferiority margin of 5%. A live birth is defined as the delivery of any surviving newborn at 28 weeks or more of gestation.

### Secondary objective

Biochemical pregnancy: defined as serum level of ß-hCG > 50 mIU/mL.Clinical pregnancy: defined as fetal heartbeat observed by vaginal ultrasound at 5 weeks after embryo transfer.Ongoing pregnancy: defined as the presence of a gestational sac and fetal heartbeat after 12 weeks of gestation.Miscarriage is defined as a condition in which the embryo or fetus does not survive and is not spontaneously absorbed or expelled from the uterus.Pregnancy complications include ectopic pregnancy, hyperemesis gravidarum, hypertensive disorders of pregnancy, gestational diabetes mellitus, preterm birth.Birth weight, including low birth weight (defined as weight < 2,500 g at birth), very low birth weight (defined as <1,500 g at birth), high birth weight (defined as >4,000 g at birth) and very high birth weight (defined as >4,500 g at birth).Large for gestational age (defined as birth weight > 90th centile for gestation, based on standardized ethnicity-based charts) and small for gestational age (defined as < 10th centile for gestational age at delivery based on standardized ethnicity-based charts).Birth defects are identifiable structural or functional defects that develop in the fetus in utero at birth.

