## Statistics

### Non-inferiority design and power calculation

A non-inferiority design is used as the new treatment, P_4_mNC-FBT, is expected to yield comparable results, but will offer significant advantages over the current standard treatment (HRT-FBT) in terms of patient convenience, reduced incidence of gestational hypertensive disorders, and lower costs as the progesterone dosage is reduced. In a previous study, the LBR is 45% in the P_4_mNC-FBT group and 39.6% in the HRT-FBT group (18). Sample sizes of 302 in P_4_mNC group and 302 in HRT group achieve 80.069% power to detect a difference of 0.05 when the non-inferiority difference is −0.05. The reference group proportion is 0.4. The treatment group proportion is assumed to be 0.35 under the null hypothesis. The power was computed for the case when the actual treatment group proportion is 0.45. The test statistic used is the one-sided Z test (unpooled). The significance level of the test is 0.05. A total of 672 patients are finally included in both groups, taking into account a 10% dropout rate.

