### Statistical analysis

ITT analyses include drop-outs and canceled cycles, PP analyses include canceled cycles but not drop-outs, and per-transfer analyses exclude both drop-outs and canceled cycles. Differences in LBR will be evaluated by means of risk differences with one-sided 95% CI (or equivalently two-sided 90% CI). Non-inferiority will be concluded if the CI excludes a difference of more than 5% in favor of the present standard treatment (HRT-FBT) in ITT and PP analyses. Depending on the characteristics of the baseline data, continuous data will be expressed as mean ± SD or median and interquartile spacing (IQR). Categorical data will be described by frequencies and percentages. The primary outcome, LBR, will be compared between the two groups using the *χ*^2^ test as well as risk ratios and 95% CI. Quantitative variables will be analyzed using the student *t*-test or Mann–Whitney test. Secondary outcomes will be compared between the two arms using the similar approach described for the primary outcome. Data will be analyzed using SPSS 26.0 and a *p*-value <0.05 will be considered statistically significant. Any missing data will be handled using pairwise deletion.

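### As worded, the definition of miscarriage counts only retained losses and leaves out those expelled or absorbed spontaneously

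*Protocol article*

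**What the plan says.** The Secondary objective section lists miscarriage as one of several secondary outcomes, in no stated order of importance, and gives it its own definition, under which "the embryo or fetus does not survive and is not spontaneously absorbed or expelled from the uterus".

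The neighbouring outcomes on the path from transfer to birth are:

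- Clinical pregnancy (same section) requires a heartbeat on ultrasound five weeks after transfer.
- Ongoing pregnancy (same section) is "defined as the presence of a gestational sac and fetal heartbeat after 12 weeks of gestation".
- Live birth (Primary objective): "A live birth is defined as the delivery of any surviving newborn at 28 weeks or more of gestation".

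The definition of miscarriage carries no gestational limit. The Statistical analysis section gives every secondary outcome a between-arm comparison: "Secondary outcomes will be compared between the two arms using the similar approach described for the primary outcome". The Data collection and management section plans one year of follow-up for all pregnancies that result from transfer.

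**The concern.** In ordinary use, miscarriage includes a pregnancy that fails and is then passed spontaneously. The definition here makes the absence of spontaneous expulsion or absorption a condition for counting the event. A coder who followed the sentence would record a missed miscarriage and would not record a complete spontaneous one.

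At stake is the validity of one reported secondary outcome. If the sentence is followed, the miscarriage rate is too low in each arm. If staff set it aside and code by usual practice, the outcome actually analysed is not the one the protocol defines. The trial is open-label, so that choice would be made by people who may know the allocation.

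**Working it through.** **1. Reading the definition case by case.** Two conditions must both hold: (a) the embryo or fetus does not survive; (b) it is not spontaneously absorbed or expelled.

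| Course of the failed pregnancy | (a) | (b) | Counted as miscarriage? |
|---|---|---|---|
| Retained in the uterus | yes | yes | yes |
| Spontaneously expelled | yes | no | no |
| Spontaneously absorbed | yes | no | no |

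Only the first row qualifies.

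**2. Is there another reading?** One could let the negation govern absorption alone, so that expelled losses count. The grammar is strained, absorbed losses would still be excluded, and the sentence would still be ambiguous. It would need rewording on either reading.

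**3. Does another section correct it?**

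- The Introduction uses the term miscarriage rate for the earlier cohort but does not define it.
- The listed pregnancy complications are ectopic pregnancy, hyperemesis, hypertensive disorders, gestational diabetes and preterm birth. None of them captures a spontaneous loss.
- Randomization and blinding refers to international diagnostic guidelines, but for subjective outcomes such as pregnancy complications. Miscarriage is listed separately from those and has its own definition.

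No section supplies a corrected definition.

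**4. Does it touch the primary analysis?** The inputs under Non-inferiority design and power calculation are proportions of 0.40 and 0.45, a margin of 0.05, a one-sided alpha of 0.05, an unpooled Z test and 302 women per arm.

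- Standard error = √[(0.40×0.60 + 0.45×0.55)/302] = √(0.4875/302) = 0.0402.
- Power = Φ(0.10/0.0402 − 1.645) = 0.8007. The plan states 80.069%.
- Inflation for dropout: 302/(1 − 0.10) = 335.6, rounded up to 336 per arm, or 672 in total, as stated.

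The figures reproduce, and miscarriage enters none of them.

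**5. Size of the undercount.** If r is the true loss rate and f the fraction of losses expelled or absorbed, the rate recorded under the literal rule is r×(1 − f). The article gives neither r nor f, so no figure follows from it.

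As illustration only, assume that 50% of 336 women have a clinical pregnancy, that 15–20% of these are lost, and that f is 30–50%. All three are assumptions with no support in the article.

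- Clinical pregnancies per arm: 336×0.50 = 168.
- Losses per arm: 168×0.15 = 25 to 168×0.20 = 34.
- Uncounted per arm: 25×0.30 ≈ 8 to 34×0.50 = 17.
- Recorded rate: from 15%×0.50 = 7.5% to 20%×0.70 = 14%, against a true 15–20%.

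What holds without these assumptions is the direction: for any f above zero, the recorded rate is too low.

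**The case against.** The best case on the other side has four parts.

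- **It is a slip in a condensed article, and everyone knows what is meant.** A slip is the likely cause. But the article does not leave the definition to another document. It states one, and the one it states excludes the ordinary case. The absence of a gestational limit or a denominator would, taken alone, be a matter for the full protocol or analysis plan, and is not part of this finding.
- **The outcome is secondary.** This stands. The definition plays no part in the live birth comparison, the 5% margin or the decision rule.
- **The losses remain partly visible.** This also stands. A woman whose pregnancy is expelled before 12 weeks can still appear as a clinical pregnancy, will be absent from ongoing pregnancy, and is not a live birth. The outcomes are not presented as an exhaustive classification, so it would be too strong to say that she disappears from the results. Subtraction does not, however, give a correct miscarriage rate, which is what the plan says it will compare.
- **The events will be recorded anyway.** Follow-up covers all pregnancies. That makes the correction cheap, but it does not make the definition right.

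A reader might also infer three stronger things that the article does not support:

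- **That miscarriage is the main secondary outcome, or the one that would explain a difference in live births.** The list is unranked.
- **That the error would bias the comparison between arms because their hormone regimens differ.** No section says that the regimens affect whether a failed pregnancy is retained or expelled.
- **That the trial's rate could not be compared with the cohort's.** The Introduction reports only that the cohort found no inferiority "in terms of clinical pregnancy rate, miscarriage rate, and LBR compared with the HRT-FBT cycle". How that study defined miscarriage is not given.

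**Conclusion.** The definition is wrong as written. Read literally, it restricts miscarriage to retained losses and would undercount the outcome in both arms whenever any loss is expelled or absorbed spontaneously. This conclusion rests on the wording and on the absence of a correction elsewhere in the article, not on an outside figure.

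The size is unknown. The range of about 8 to 17 uncounted losses per arm shows only what the assumed rates would produce. No difference in the undercount between arms can be claimed. The effect is confined to one secondary outcome, and the non-inferiority conclusion on live birth and the sample size stand. It should be corrected before outcomes are coded, but it does not threaten the trial's main result.

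**What to change.** Replace the sentence with: *Miscarriage: loss of an intrauterine pregnancy before 28 completed weeks of gestation, whether retained, spontaneously expelled or absorbed.* The 28-week limit is the one already used for live birth under Primary objective. If retained losses are of separate interest, report missed miscarriage as a sub-category.

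The term intrauterine pregnancy is deliberate. Limiting the definition to loss of a clinical pregnancy would require a heartbeat at the five-week scan. It would therefore drop retained losses without a heartbeat at that scan, which the present wording includes.

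The cost is a one-sentence amendment and a check that the case report form records every loss with its gestational age and whether it was retained, expelled or absorbed. No further follow-up is needed, because all pregnancies are already to be followed.

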## Methods and analysis

### Study design

This study protocol describes the design of a single-center, open-label, randomized, controlled trial. Patients will be recruited from the reproductive center of the Affiliated Hospital of Shandong University of Traditional Chinese Medicine (SDUTCM). To ensure procedural consistency, all participating investigators will receive uniform training and have regular communication. The study is registered at ClinicalTrials.gov (ID: NCT06644794) in 15 October 2024. Patient enrollment will begin in December 2024 and is scheduled to continue until June 2027. Patients will be randomly assigned to P_4_mNC cycles and HRT cycles. This study has been approved by the Institutional Review Board of Affiliated Hospital of SDUTCM (Reference No. 2024-144-KY). Informed consent will be obtained from each patient before any study procedure (Figure 1).

**Figure 1 fig1:**
[figure not shown]
The study flow chart. MC, the menstrual cycle; P_4_mNC, progesterone modified natural cycle; FBT, frozen–thawed blastocyst transfer. HRT, hormone replacement therapy.

### Patient and public involvement

Lack of patient and public involvement in the formulation of research questions, study design or recruitment, and study conduct and reporting (Figure 2).

**Figure 2 fig2:**
[figure not shown]
Scheme of endometrial preparation in progesterone modified natural and hormone replacement therapy cycles. ET, embryo transfer; mP4, micronized progesterone; *β*-hCG, beta human chorionic gonadotropin; P4mNC, progesterone modified natural cycle; HRT, hormone replacement therapy.

### Study population and recruitment

A total of 672 women undergoing autologous single FBT at the reproductive center of the Affiliated Hospital of SDUTCM will be recruited. Prior to initiating treatment, investigators will browse the files of patients scheduled for FET and screen them including uterine and ovarian ultrasound on day 2 or 4 of their menstrual cycle to ensure that enrollment criteria are met. Details about the trial will be presented at their first visit. After obtaining approval from the ethics committee, all women will provide written informed consent prior to participation. At any time during the study, the patient can withdraw without reason.

### Eligibility criteria

#### Inclusion criteria

Patients aged 21 to 44 years undergoing FBT;Body mass index (BMI) 18–35 kg/m^2^;Having regular ovulatory cycles.

#### Exclusion criteria

Untreated uterine adhesions;Medical contraindications to estrogen and progesterone therapy;Illnesses contraindicating assisted reproductive technology or pregnancy;History of recurrent implantation failures (> 2 embryo transfer failures);

### Treatment and interventions

Patients will undergo ovarian stimulation and oocyte retrieval according to the protocol of the attending physician. Final oocyte maturation will be induced using recombinant hCG (250 μg, Ovitrelle, Serono, France) or GnRH agonist (0.1 mg, Triptoreline, Decapeptyl, Ipsen, France). After 35–36 h, oocyte retrieval is performed transvaginally under ultrasound guidance. Within 2–6 h, all retrieved oocytes will be fertilized by either IVF or intracytoplasmic sperm injection (ICSI), and all embryos will be cultured to blastocyst stage. Based on the Gardner classification, a morphological quality score will be assigned to blastocysts. We divide embryos into two groups: blastocysts of good quality with an ICM/TE score type AA, AB, BA, or BB; and poor-quality blastocysts with an ICM/TE score AC or BC. Vitrified-warmed embryos will be transferred in one of two types of cycles: P_4_mNC or HRT.

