### Randomization and blinding

Statistical professionals not involved in the study will complete the randomization groupings using software (R 4.0.0, R Foundation for Statistical Computing, Vienna, Austria), and stratify by female age (<35 or ≥35 years). Patients will then be randomized in a 1:1 ratio to the P_4_mNC-FBT and HRT-FBT groups. Both the investigators and patients will be aware of the allocation. Blinding of the intervention is impossible for patient and doctors administering it. To minimize performance and reporting biases arising from the absence of blinding, embryologists and doctors involved in embryo transfer are blinded to the group assignments of the participants. Subjective outcomes, such as pregnancy complications, were assessed by strictly adhering to internationally recognized diagnostic guidelines to ensure objectivity. Additionally, patients received standardized instructions for symptom reporting to avoid discrepancies in self-described experiences.

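### The two blastocyst-quality classes leave out CA, CB and CC, and the article's primary analysis makes no use of quality, at a small cost in precision

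*Protocol article*

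**What the plan says.** Under Treatment and interventions, the protocol article states that "a morphological quality score will be assigned to blastocysts" on the Gardner system. It then names two classes: "blastocysts of good quality with an ICM/TE score type AA, AB, BA, or BB", and "poor-quality blastocysts with an ICM/TE score AC or BC". These cover six of the nine combinations of inner cell mass (ICM) and trophectoderm (TE) grade. The other three (CA, CB, CC) are not mentioned, and neither the inclusion nor the exclusion criteria refer to embryo quality.

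The classes do not appear again. Under Randomization and blinding, the plan is to "stratify by female age (<35 or ≥35 years"; no other factor is named. Under Statistical analysis, the deciding comparison is given as follows: "Differences in LBR will be evaluated by means of risk differences with one-sided 95% CI (or equivalently two-sided 90% CI". In addition, live birth "will be compared between the two groups using the *χ*^2^ test as well as risk ratios and 95% CI". No covariate is named for any of these analyses.

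**The concern.** Each woman receives a single blastocyst, and the article admits both quality classes. Morphological grade is therefore a natural candidate for a prognostic covariate. It is known before transfer, the laboratory already holds it, and the embryologists are to be blinded to allocation, so it is little exposed to open-label bias. When such a value is left out, the variation it explains stays in the standard error of the risk difference. That matters somewhat here because the margin is only 5 points and planned power is only just above 80%.

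The gap in the classes comes first in practice. A covariate with three undefined levels cannot be prespecified, and a ruling on CA, CB and CC made after outcomes are known would be a data-dependent choice.

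**Working it through.** **1. The plan's own figure.** Inputs from Non-inferiority design and power calculation: live-birth rates 0.40 (HRT) and 0.45 (P4mNC), margin 0.05, one-sided alpha 0.05, unpooled Z test, 302 per arm.

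- SE = √[(0.40×0.60 + 0.45×0.55)/302] = √(0.4875/302) = 0.04018
- Power = Φ(0.10/0.04018 − 1.645) = Φ(0.844) = 80.07%
- With 10% dropout: 302/0.90 = 335.6, so 336 per arm and 672 in total

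The stated 80.069% and 672 are reproduced. This point does not touch the sample size.

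**2. Gain from adjustment.** Two inputs are needed that the article does not give, so both are assumptions: the poor-quality share q (0.10 to 0.50) and the live-birth gap d between good and poor quality (0.05 to 0.25).

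- Share of outcome variance explained: R² = q(1−q)d² / [p(1−p)], with p = 0.425 (mean of 0.40 and 0.45), so p(1−p) = 0.2444
- Adjusted SE = 0.04018 × √(1−R²)
- 90% CI half-width before adjustment = 1.645 × 4.018 = 6.61 points
- Equivalent number per arm without adjustment = 302/(1−R²)

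| q | d | R² | Power | CI half-width narrows by | Equivalent n per arm |
|---|---|---|---|---|---|
| 0.10 | 0.05 | 0.09% | 80.1% | 0.003 points | 302 |
| 0.30 | 0.20 | 3.44% | 81.3% | 0.11 points | 313 |
| 0.50 | 0.25 | 6.39% | 82.3% | 0.21 points | 323 |

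For the middle row: 0.30×0.70×0.20² = 0.0084, and 0.0084/0.2444 = 3.44%. The adjusted SE is 0.04018×0.9827 = 0.03948, and Φ(0.10/0.03948 − 1.645) = 81.3%.

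**3. Whether chance imbalance is an extra problem.** At 336 per arm, the SD of the between-arm difference in poor-quality share is √[2q(1−q)/336]. With q = 0.30 this is 3.54 points. With d = 0.20, one SD moves the crude risk difference by 0.71 points.

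The crude SE at 336 per arm is √(0.4875/336) = 3.81 points. The imbalance therefore contributes 0.71²/3.81² = 0.50/14.5, about 3.4% of the variance. This matches R² in step 2: it is the same variation, already counted in the crude standard error.

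**4. Size of that shift over the assumed range.** One SD gives 0.12–0.96 points (2–19% of the margin), and 1.96 SD gives 0.23–1.89 points (5–38%). With a gap of 15 points or less, even 1.96 SD stays below a quarter of the margin (1.25 points). At q = 0.30 and d = 0.20, the 1.96-SD shift is 1.39 points (28%), and the probability of a shift above 1.25 points is 7.7%.

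**The case against.** The strongest case against is that nothing in the primary analysis is wrong. A crude risk difference with a one-sided 95% limit is valid under randomisation. Covariates are commonly settled in a statistical analysis plan, which is not shown, and the gain is small by any reckoning. The article may also list only six grades because no others are transferred.

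Most of this stands. The article does state its primary method, however, and that method is unadjusted, so the point is a cheap improvement on stated text and not a complaint about missing detail. The six-grade reading is possible, but the article does not say so.

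Three stronger readings are tempting and are not supported:

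- **Chance imbalance in quality could move the result by more than a quarter of the margin and so threatens the conclusion.** That size needs an assumed gap of about 20 points or more and an imbalance near its 95% limit. More fundamentally, the crude standard error already contains this variation. It causes no bias and does not raise the type I error.
- **Women with CA, CB or CC blastocysts would be lost through the pairwise-deletion rule.** The article plans no comparison by quality, so nobody drops out, and the primary outcome does not depend on the class.
- **Quality is graded for every woman and is never analysed.** The text says that blastocysts are scored, not that every woman has a value. Its silence on further use holds for this article only.

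**Conclusion.** The point holds in modest form. The two classes are incomplete as written, and the article gives a pre-transfer value that is probably prognostic no role in stratification or in the primary analysis. The cost is precision only: about 0.1–6% of the variance, or between zero and about 2 percentage points of power (80.1% to at most 82.3%).

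These figures rest on the assumed ranges for the poor-quality share and the live-birth gap, since the article reports neither. They also assume that quality adds information beyond age. They apply to whichever quality measure is used: the best grade on file may have a smaller poor-quality share or a smaller gap than the grade of the transferred embryo, which would put the gain lower in the range. The validity of the planned analysis, the margin and the sample size are not affected.

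**What to change.** 1. **Complete the classes for analysis.** For example, count any C in ICM or TE as poor quality, or state whether blastocysts with ICM grade C are used in the trial. This concerns the analysis variable only; which blastocysts are transferred is for the investigators to state.
2. **Fix the covariate before allocation.** Record the best grade among the vitrified blastocysts on file at randomisation. The grade of the transferred embryo would be missing for cancelled cycles, which the article keeps in both the ITT and PP sets. Women are screened from those scheduled for frozen transfer, so the grade should normally be available by then. The plan should confirm this and give a rule for any woman without one.
3. **Prespecify its use.** Include it in the primary ITT and PP analyses by logistic regression, standardised to a marginal risk difference. Keep the 5-point margin and the one-sided 95% (two-sided 90%) interval rule. The crude risk difference can be reported beside it.

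The cost is one baseline field that the laboratory already holds, a few lines of analysis text, and one standardisation step in place of a two-by-two table, with the software for that step named. No extra patients or visits are needed. The change should be made before outcome data by arm are seen.
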